### Study Measures

Data collection includes sociodemographic variables and validated questionnaires in Spanish to assess the primary and secondary study outcomes.

#### Primary Variables

The primary variables include LTPA, OPA, and work ability. LTPA and OPA are assessed using the Spanish version of the Global Physical Activity Questionnaire [41]. This tool assesses PA in 3 domains: occupational, active transport, and leisure, yielding weekly metabolic equivalent of task (MET) minutes for each. MET minutes are calculated by multiplying activity duration by the standard MET values.

The official Spanish version of the questionnaire, endorsed by the WHO, has shown good test-retest reliability (intraclass correlation coefficient=0.70-0.90) and moderate concurrent validity (Spearman ρ≈0.42) compared with the accelerometry in European and Latin American Spanish-speaking populations. Although it has not been formally validated in Spain, its widespread international use and standardization support its inclusion in this study [42].

Work ability is being assessed with the Spanish version of the Work Ability Index (WAI) [43]. The WAI measures 7 dimensions: current work ability compared to lifetime best, work ability in relation to job demands, physician-diagnosed illnesses, estimated work impairment due to illness, sick leave over the past year, prognosis of work ability over the next 2 years, and mental resources. Total scores classify work ability into 4 categories: poor (7-27), moderate (28-36), good (37-43), and excellent (43,45-49). The WAI has been adapted and endorsed by the Spanish National Institute for Safety and Health at Work (NTP 1147) for the Spanish occupational context [43]. It was validated in a sample of 1184 Spanish health center workers, demonstrating satisfactory reliability (intraclass correlation coefficient>0.75), a stable 2-factor structure, and convergent validity with measures of health and productivity, reflecting strong psychometric properties in occupational settings [44].

#### Secondary Variables

Secondary variables include the prevalence of MSDs, HRQoL, and physical and mental workload. MSDs are being evaluated using the Spanish version of the Standardized Nordic Questionnaire [45], which identifies symptoms across various anatomical regions and their functional impact. It includes symptom checklists and related consequences, such as reduced activity or health care visits. This questionnaire has been validated across multiple Spanish occupational samples. In a study of 526 nursing assistants in Asturias, the questionnaire demonstrated good test-retest reliability (Cohen κ=0.60-0.81) and internal consistency (Kuder-Richardson 20=0.74-0.87) [46]. In addition, in a separate validation among 312 professional musicians in Madrid, similar values were observed (Cohen κ=0.60-0.81; Kuder-Richardson 20=0.737-0.873), and construct validity was supported by significantly higher disability and pain scores in anatomical regions with reported symptoms [45]. The tool also demonstrated high feasibility, with an average completion time of 6 (SD 2) minutes [45].

HRQoL is being assessed using the Short Form-12 Health Survey [47], which covers 8 health dimensions across physical and mental domains. Scores are standardized to a population mean of 50 (SD 10); scores greater than 50 indicate better-than-average perceived health. The Short Form-12 Health Survey, validated in a representative Spanish adult population (n≈11,000), reported high internal consistency (Cronbach α=0.87 for the physical component summary and Cronbach α=0.86 for the mental component summary). It accounted for more than 90% of the variance observed in the Short Form-36 Health Survey, further supporting its reliability and construct validity for assessing HRQoL [48].

Workload is being evaluated using the National Aeronautics and Space Administration Task Load Index [49], which includes 6 subscales: mental, physical, and temporal demand, performance, effort, and frustration. After weighting each subscale, participants rate them on a scale of 0 to 100. Weighted scores are averaged to compute a total workload score. This index has been validated in Spain in a sample of 398 workers across 7 occupational sectors. The instrument demonstrated strong internal consistency (Cronbach α>0.80) and confirmed its intended factorial structure, supporting its suitability for assessing perceived workload in diverse occupational groups [50]. The Instituto Nacional de Seguridad y Salud en el Trabajo recommends its use to estimate perceived mental workload in real work environments due to its sensitivity to variation in cognitive and physical demands and its nonintrusive nature (NTP 544) [49].

Sociodemographic data collected include age, sex, gender, menopause status and related symptoms (if applicable), anthropometric variables, education level, work role (PTGAS, PDI, and PI), work schedule (split, continuous, or mixed), workday type (full time or part time), gross annual income, and number of cohabitants.

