### Objectives

On the basis of the aforementioned background, the primary objective of this study is to analyze the relationship between LTPA and work ability among university staff in the CAM, considering the potential modifying effect of OPA, and exploring differences by sex and gender. The secondary objectives are to (1) determine the prevalence of MSDs in this population and analyze their association with LTPA and OPA levels using validated questionnaires; (2) evaluate the relationship between both domains of PA and perceived physical and mental workload, adjusting for occupational role and sociodemographic factors; (3) examine the association between LTPA and OPA and self-perceived health-related quality of life (HRQoL); and (4) explore whether these associations vary according to sex, gender, and occupational category.

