### Planned Data Analysis

Descriptive analyses will summarize all variables, reporting means, medians, SDs, and quartiles for continuous variables and frequency distributions for categorical variables. Normality will be assessed using the Kolmogorov-Smirnov test.

To examine associations between PA levels (both OPA and LTPA) and the primary outcomes (work ability, musculoskeletal health, and quality of life), multiple linear and logistic regression model analyses will be performed, depending on the nature of the outcome variable. These models will adjust for relevant covariates, including age, sex, occupational group, and key social determinants of health. Moderation by gender will be assessed through the inclusion of interaction terms, and stratified analyses by sex and gender will be conducted to explore potential differential effects.

To account for the expected heterogeneity across occupational roles, key analyses will be stratified by job category (PDI or PI vs PTGAS). Occupational role will also be included as a covariate in multivariable regression models to adjust for its potential confounding effect. In addition, subgroup analyses will be conducted to explore interaction effects between occupational role and levels of OPA and LTPA on primary and secondary outcomes, including work ability, MSDs, perceived workload, and HRQoL. PA levels will be categorized using WHO-recommended cutoffs, with high PA defined as 600 MET-minutes per week or more, allowing for group comparisons (eg, high vs low OPA or LTPA) in relation to health and occupational outcomes.

Furthermore, mediation analyses will be conducted to evaluate whether MSDs mediate the relationship between PA and work ability. These analyses will follow sequential multiple regression models, applying the approach described by Preacher [51] and Hayes [52] and adapted for cross-sectional data. Model fit will be assessed using the *R*² coefficient and *F* test. Statistical significance will be set at *P*<.05, and 95% CIs will be reported for all regression coefficients.

This analytical approach aligns with a gender-sensitive framework, enabling the detection of differential effects and the potential moderating roles of gender in the relationships between PA, occupational factors, and health outcomes.

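### Objective 2 asks for adjusted associations with physical and mental workload, but the protocol derives only one pooled NASA-TLX total and leaves workload out of its list of adjusted-regression outcomes

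*Protocol article*

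**What the plan says.** Four places in the protocol article bear on this.

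- **Objectives**, second secondary objective: "evaluate the relationship between both domains of PA and perceived physical and mental workload, adjusting for occupational role and sociodemographic factors".
- **Secondary Variables**, opening sentence: "Secondary variables include the prevalence of MSDs, HRQoL, and physical and mental workload".
- **Secondary Variables**, workload instrument: the NASA-TLX, "which includes 6 subscales: mental, physical, and temporal demand, performance, effort, and frustration". On scoring: "After weighting each subscale, participants rate them on a scale of 0 to 100", and then "Weighted scores are averaged to compute a total workload score". No other workload score is described. The same paragraph reports that the Spanish occupational safety institute "recommends its use to estimate perceived mental workload in real work environments".
- **Planned Data Analysis**: for the association of OPA and LTPA with "the primary outcomes (work ability, musculoskeletal health, and quality of life), multiple linear and logistic regression model analyses will be performed". The next sentence attaches the covariates (age, sex, occupational group, social determinants) to these models. Perceived workload is named later in that section, among the outcomes of subgroup analyses that look for interaction between occupational role and OPA or LTPA. No covariate set is given there. High-versus-low activity comparisons are also planned, for outcomes described only in general terms.

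**The concern.** There are two mismatches, both between statements that are in the text.

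**Outcome.** The objective and the list of secondary variables name physical and mental workload. The derived variable is a single figure pooled over six subscales, four of which are neither physical nor mental demand, and the text supports the index as a measure of mental workload. Nothing in the plan is designated as the physical-workload outcome.

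**Model.** The objective asks for adjustment for role and sociodemographic factors. Of the three secondary variables, musculoskeletal disorders and quality of life enter the list of adjusted-regression outcomes, and workload alone does not.

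The study's rationale contrasts cognitively loaded, sedentary work with jobs that need more physical effort, so it is reasonable to expect physical and mental demand to relate differently to OPA. A null or small association with the pooled total could then hide a clear association with one component. A positive one could not be attributed to either. If subscales are chosen only after the data are seen, the result for this objective becomes a post hoc selection.

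**Working it through.** **1. Objective against plan**

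| Objective 2 requires | The article provides |
|---|---|
| Physical workload as an outcome | No designated score; physical demand is one of six parts of the total |
| Mental workload as an outcome | No designated score apart from the total |
| Association with LTPA and OPA | Interaction of role with OPA and LTPA, in subgroup analyses |
| Adjustment for role | Role is part of the interaction analysis by construction |
| Adjustment for sociodemographic factors | Stated for three other outcomes, not for workload |

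**2. What a pooled total does**

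The protocol gives no weights and no expected effects, so all the inputs in this step are assumptions. Write the total as T = Σ(wᵢxᵢ)/Σwᵢ, with each xᵢ on 0 to 100.

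Equal weights, 1/6 each:
- Physical demand +12, others 0: 12/6 = 2.00.
- Mental demand +12, others 0: also 2.00.
- Physical +6 and mental +6: (6 + 6)/6 = 2.00.
- Physical +10, others 0: 10/6 = 1.67.
- Physical +10 and mental −5: 5/6 = 0.83.
- Physical +10 and mental −10: 0/6 = 0.00.

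The first three patterns differ, yet the total cannot tell them apart.

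Unequal weights summing to 15, with physical +10 and mental −10:

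| Weights physical/mental | Shift in total |
|---|---|
| 0/5 | −50/15 = −3.33 |
| 1/4 | (10 − 40)/15 = −2.00 |
| 2/3 | (20 − 30)/15 = −0.67 |
| 5/1 | (50 − 10)/15 = +2.67 |

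With opposing effects, both the size and the sign of the shift depend on the weights. Exact cancellation needs weight times effect to be equal and opposite.

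**3. What dilution does to power (illustration)**

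The sample-size section gives a minimum of 796, which reproduces: n₀ = 1.96² × 0.25/0.03² = 1067.1, and 1067.1/(1 + 1066.1/3117) = 795.1, rounded up to 796. Take 796 split evenly into high and low activity (398 each, assumed) and a two-sided 5% test. Then power ≈ Φ(δ/SE − 1.96), with SE = SD × √(2/398) = SD × 0.0709.

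- Physical-demand subscale, δ = 10, SD 25 (assumed): SE = 1.77, power above 99%. With SD 30 it is still above 99%.
- Total, δ = 1.67, SD 15 (assumed): SE = 1.06, Φ(1.57 − 1.96) ≈ 35%. The range is about 65% with SD 10 to about 22% with SD 20.
- Total, δ = 0.83, SD 15: Φ(0.78 − 1.96) ≈ 12%.

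With a 30:70 split and the same central SDs, the three figures are above 99%, about 30% and about 11%. These figures are unadjusted and rest wholly on the assumed effects and SDs. They show the direction and rough scale of the loss and do not predict it.

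**The case against.** **The scoring sentence describes the instrument and does not say that only the total will be analysed.** This is correct, and the 0-to-100 ratings are collected. A reader might infer that Objective 2 cannot be answered. That does not follow: the data will be there. What stands is that no workload outcome other than the total is named.

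**Workload is in the analysis.** It is. A reader might infer from the regression list that workload was dropped altogether, but Planned Data Analysis names it in the role-by-activity subgroup analyses, and the general high-versus-low comparisons may cover it. That section also says, without limiting it by outcome, that role will be a covariate in multivariable models. None of this supplies the adjusted main association: the subgroup analyses aim at interaction, no sociodemographic covariates are attached to them, and no multivariable model is named for workload.

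**Opposing effects are not documented.** True. The Discussion describes high physical and mental workload moving together with lower LTPA, and stratifying by job category would remove much of an OPA contrast that lies between roles. A reader might infer that opposite effects will cancel in the total. The documents give no effect directions, and exact cancellation is a special case. The milder problem remains: even when both components move the same way, the total cannot say which one carries the association, and physical demands can still vary within a job category.

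**Physical and mental workload could be read as one composite.** This is possible, since the article credits the index with sensitivity to both cognitive and physical demands. It does not settle the regression list, which omits workload under either reading.

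**This is a condensed article, and its Results section refers to a predefined statistical plan that is not shown.** Subscale scoring may well be specified there. The point does not rest on missing scoring detail alone: the objective asks for an adjusted workload analysis, and the article's stated list of adjusted-regression outcomes does not contain it.

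**Conclusion.** The point holds in a limited form. Followed as written, the plan does not deliver what Objective 2 asks for: it designates no physical-workload outcome, and its only workload score is a pooled total. It states no covariate-adjusted main-association model for workload. The accurate description of the statistical effect is dilution or masking. Under assumed equal weights, a single-subscale shift appears in the total at one sixth of its size (12 points become 2). Under the assumed opposing effects, the shift in the total ranges from −3.33 to +2.67 according to the weights.

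The mismatch between the objective and the list of regression outcomes needs no assumption. The size of the dilution depends on weights, effects and SDs that the documents do not give. One secondary objective is affected. The primary objective, on LTPA and work ability, is not.

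**What to change.** Align Objectives, Secondary Variables and Planned Data Analysis:

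1. Under Secondary Variables, name the 0-to-100 mental-demand and physical-demand ratings as separate outcomes for Objective 2, reported beside the weighted NASA-TLX total. The total need not be dropped.
2. Under Planned Data Analysis, add workload to the outcomes of the adjusted linear models, with LTPA and OPA as exposures and role, age, sex and the social determinants as covariates.
3. Keep the role-by-activity interaction analyses for workload as the follow-up question to that main association.

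The two subscales cost two extra regressions on items already in the form. The total, if not already modelled, takes one more of the same specification. With both exposures in each subscale model, that is 2 × 2 = 4 further coefficients at the 5% level, or 4 × 0.05 = 0.2 expected false positives if all four associations are null. This is a small addition to the multiplicity, to be acknowledged when the results are reported. The article states that no analysis has been run and that collection continues to June 2027, so the change can still be made as a pre-specification.

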### Data Collection

Data collection began after receiving ethics approval in November 2024 (clinical research ethics committee: CEID/2024/3/061). At the time of manuscript submission, no statistical analyses had been conducted; this protocol describes the planned methodology in detail in accordance with the journal’s protocol submission requirements. Participants are completing an ad hoc online form created in Microsoft Forms, accessible on any internet-enabled device. The form includes all questionnaires and measures described earlier. Completion time is approximately 25 minutes. To optimize response rates and minimize perceived burden, this estimated completion time is clearly communicated in the invitation message. This duration was deemed acceptable for participants to balance respondent convenience with the need for comprehensive data collection. To further support participation, reminder messages will be sent at regular intervals to prompt responses and ensure questionnaire completion.

Data are stored automatically in a secure Microsoft Excel database, accessible only to the principal investigator, who ensures data completeness and accuracy, oversees coding, and securely maintains the dataset for subsequent statistical analysis.

### Planned Data Analysis

Descriptive analyses will summarize all variables, reporting means, medians, SDs, and quartiles for continuous variables and frequency distributions for categorical variables. Normality will be assessed using the Kolmogorov-Smirnov test.

To examine associations between PA levels (both OPA and LTPA) and the primary outcomes (work ability, musculoskeletal health, and quality of life), multiple linear and logistic regression model analyses will be performed, depending on the nature of the outcome variable. These models will adjust for relevant covariates, including age, sex, occupational group, and key social determinants of health. Moderation by gender will be assessed through the inclusion of interaction terms, and stratified analyses by sex and gender will be conducted to explore potential differential effects.

To account for the expected heterogeneity across occupational roles, key analyses will be stratified by job category (PDI or PI vs PTGAS). Occupational role will also be included as a covariate in multivariable regression models to adjust for its potential confounding effect. In addition, subgroup analyses will be conducted to explore interaction effects between occupational role and levels of OPA and LTPA on primary and secondary outcomes, including work ability, MSDs, perceived workload, and HRQoL. PA levels will be categorized using WHO-recommended cutoffs, with high PA defined as 600 MET-minutes per week or more, allowing for group comparisons (eg, high vs low OPA or LTPA) in relation to health and occupational outcomes.

Furthermore, mediation analyses will be conducted to evaluate whether MSDs mediate the relationship between PA and work ability. These analyses will follow sequential multiple regression models, applying the approach described by Preacher [51] and Hayes [52] and adapted for cross-sectional data. Model fit will be assessed using the *R*² coefficient and *F* test. Statistical significance will be set at *P*<.05, and 95% CIs will be reported for all regression coefficients.

This analytical approach aligns with a gender-sensitive framework, enabling the detection of differential effects and the potential moderating roles of gender in the relationships between PA, occupational factors, and health outcomes.

The online questionnaire is programmed so that all questions must be completed before submission, thereby minimizing the likelihood of missing data. Consequently, the proportion of missing values is expected to be negligible. In the unlikely event that incomplete data are detected (eg, due to technical errors or partial dropouts), a descriptive analysis of missingness will be performed. In such cases, listwise deletion will be applied.

All analyses will be conducted using SPSS Statistics (version 27.0; IBM Corp) by a blinded statistician working with coded data.

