**Results:**

This study was approved by the ethics committee of the University of Alcalá in November 2024. Recruitment began in December 2024 and will continue until June 2027. Data analysis will be conducted progressively. Results will be disseminated in peer-reviewed journals and presented at scientific conferences following gender-sensitive and transparent reporting standards.

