## Results

This study was approved by the clinical research ethics committee of the UAH in November 2024 (CEID/2024/3/061), in compliance with the European data protection regulations. Recruitment began in December 2024 and is currently ongoing. As of July 2025, data collection was actively underway and is expected to continue until June 2027, the planned study completion date. Participants are completing the online questionnaire using Microsoft Forms, as detailed in the Methods section.

All responses are automatically collected and securely stored in a cloud-based spreadsheet accessible only to the principal investigator. Preliminary checks are being performed to ensure data completeness and consistency. No statistical analyses have been conducted to date, as data collection is still ongoing.

Upon completion of data collection, the final dataset will be analyzed following the predefined statistical plan. Study results, irrespective of their significance, will be disseminated in peer-reviewed national and international journals and presented at academic conferences. The dissemination strategy will adhere to the principles of a gender-sensitive and transparent reporting approach, aligned with current research integrity and open science standards.

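### The analysis section calls three outcomes primary, where the rest of the protocol has only work ability, and it states no LTPA×OPA test although the primary objective needs one

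*Protocol article*

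**What the plan says.** **Outcome hierarchy.** The Objectives section states that "the primary objective of this study is to analyze the relationship between LTPA and work ability among university staff in the CAM", with OPA as a potential modifier and differences by sex and gender to be explored. The associations of physical activity with MSDs and with HRQoL are secondary objectives 1 and 3. Under Primary Variables: "The primary variables include LTPA, OPA, and work ability". Of these, only work ability is an outcome. Under Secondary Variables: "Secondary variables include the prevalence of MSDs, HRQoL, and physical and mental workload". Planned Data Analysis instead gives the purpose of its regressions as: "To examine associations between PA levels (both OPA and LTPA) and the primary outcomes (work ability, musculoskeletal health, and quality of life".

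**Tests.** Planned Data Analysis applies linear or logistic regression to both OPA and LTPA. The interactions it describes are with gender and with occupational role. It adds strata by sex, gender and job category, and a mediation analysis. One level is given for all of this: "Statistical significance will be set at *P*<.05", with 95% CIs for all regression coefficients.

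**Timing.** The abstract says: "Data analysis will be conducted progressively". The Results section says: "Upon completion of data collection, the final dataset will be analyzed following the predefined statistical plan". Both Data Collection and Results state that no analysis has yet been done.

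**The concern.** The label primary decides which result the study may lead with. If the analysis section is followed literally, a significant association of either exposure with MSDs or HRQoL could be presented as a primary finding, and the protocol would support it. So could an OPA coefficient, although the primary objective makes LTPA the exposure and OPA the modifier.

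Conversely, the one test that would answer the second half of the primary objective, whether OPA modifies the association of LTPA with work ability, does not appear in the analysis section. The question behind the physical activity paradox thus has no stated test, while outcomes described elsewhere as secondary are promoted. In addition, two statements on when analysis takes place do not agree.

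**Working it through.** **1. Does the sample size identify a primary test?**

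Inputs from Sample Size: N = 3117, margin e = 0.03, p = 0.5, 95% confidence (z = 1.96), 10% dropout.

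- n = N·z²·p(1−p) / [e²(N−1) + z²·p(1−p)] = 3117 × 0.9604 / (0.0009 × 3116 + 0.9604) = 795.1, rounded up to 796.
- 796 / 0.9 = 884.4, rounded up to 885.

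Both stated figures reproduce. The calculation is for the precision of a single proportion. It contains no hypothesis, effect size or number of tests, so it does not settle which outcome or coefficient is primary.

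**2. The sections side by side**

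| Item | Objectives; Primary and Secondary Variables | Planned Data Analysis |
|---|---|---|
| Work ability | primary | primary |
| MSDs | secondary | primary |
| HRQoL | secondary | primary |
| LTPA | exposure in the primary objective | exposure |
| OPA | modifier in the primary objective | exposure, equal to LTPA |
| LTPA×OPA on work ability | part of the primary objective | not stated |

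The MSD and HRQoL rows cannot both be right. Later in Planned Data Analysis, work ability, MSDs, workload and HRQoL are listed together as primary and secondary outcomes without saying which is which. The text therefore does not correct itself.

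**3. Size if read as written**

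The minimum count is 3 outcomes × 2 exposures = 6 coefficients, each at 0.05. With all nulls true and independent tests, the family-wise error is 1 − 0.95^k:

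- k = 1 (LTPA on work ability only): 5.0%
- k = 3 (three outcomes, one exposure): 1 − 0.95³ = 14.3%
- k = 6: 1 − 0.95⁶ = 26.5%

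The document gives no correlation between tests. As an assumed range, six equicorrelated normal test statistics give 24% at a correlation of 0.3, 21% at 0.5 and 16% at 0.7. Interactions, strata and mediation are not counted.

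**4. Two primary tests**

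If LTPA on WAI and LTPA×OPA on WAI were both primary at 5% each, the rate under independence would be 1 − 0.95² = 9.75%. Naming both is therefore not enough; they need an order or a split of alpha.

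**5. Timing**

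The abstract's sentence follows directly on the statement that recruitment continues to June 2027, but it does not itself say that data will be analysed during recruitment. The Results section places analysis of the final dataset after data collection. The wordings differ, and neither mentions an interim look, a stopping rule or a sample size that depends on results.

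**The case against.** The strongest reply is that the hierarchy can be recovered. The abstract's objective, Objectives, Primary Variables, Secondary Variables and Anticipated Findings all point to LTPA and work ability as the primary question, and one parenthesis is out of line. This stands. It rules out the stronger reading that the study has no primary question, or that no error-controlled primary claim is possible: a single pre-named LTPA coefficient on WAI would need no adjustment. It does not remove the contradiction, because the odd parenthesis sits in the section that governs the analysis.

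Second, this is a condensed article. A multiplicity method is commonly left to a statistical analysis plan, and the Results section refers to a predefined one. This also stands, so the lack of a named adjustment method is not part of the point. A separate plan could add detail, but it could not make both outcome lists in this article correct.

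Third, the study is descriptive and cross-sectional, and Strengths and Limitations calls its objectives exploratory. That lowers the severity. The same section, however, claims adequate power to detect significant associations, so claims of significance are intended.

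Fourth, independence is implausible. The WAI itself scores diagnosed illness and impairment from illness, and MSDs are modelled as a mediator of work ability. Hence 26.5% is best read as a ceiling under positive correlation.

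A reader might also infer from the word used in the abstract that repeated looks or optional stopping are planned. The documents do not show this. Staged analysis or reporting after closure is an equally possible meaning, and any figure for inflation from repeated looks would need a number of looks that appears nowhere.

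**Conclusion.** The contradiction holds: MSDs and HRQoL are primary in Planned Data Analysis and secondary in Objectives and Secondary Variables. The same section raises OPA from modifier to co-equal exposure and omits the interaction that the primary objective calls for. Read literally, six tests at 5% could each support a primary claim, with a family-wise error of about 26.5% under independence and all nulls true, and roughly 16% to 24% over the assumed correlations of 0.7 to 0.3. Read through the other sections, the main LTPA test is a single test at 5%. The timing statements need to be reconciled, but they carry no demonstrated error inflation. Severity: should-fix.

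**What to change.** In Planned Data Analysis:

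- Name WAI as the primary outcome, and MSDs, HRQoL and workload as secondary outcomes.
- Name the LTPA coefficient on WAI as the primary test. State the LTPA×OPA term on WAI as the next test in a fixed order, tested for a claim only if the first succeeds, or split alpha between the two (for example 0.025 each).
- Label all other associations, interactions, strata and mediation results as secondary or exploratory, reported with confidence intervals.

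In the abstract and the Results section, give one consistent statement of when analysis takes place. If progressive refers to staged reporting after data collection, say so.

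The cost is mostly wording, but adding the interaction term and the testing order is a small change to the analysis. Because no data have been analysed, it can still be fixed in advance. The downside is that fewer results may be called primary or significant.
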